## Abstract

**Background:**

Ecological momentary assessment (EMA) of mental health symptoms may influence the symptoms that it measures, i.e. assessment reactivity. In the field of depression, EMA reactivity has received little attention. We aim to investigate whether EMA of depressive symptoms induces assessment reactivity. Reactivity will be operationalised as an effect of EMA on depressive symptoms measured by a retrospective questionnaire, and, secondly, as a change in response rate and variance of the EMA ratings.

**Methods:**

This study is a 12-week randomised controlled trial comprising three groups: group 1 carries out EMA of mood and completes a retrospective questionnaire, group 2 carries out EMA of how energetic they feel and completes a retrospective questionnaire, group 3 is the control group, which completes only the retrospective questionnaire. The retrospective questionnaire (Centre for Epidemiologic Studies Depression scale; CES-D) assesses depressive symptoms and is administered at baseline, 6 weeks after baseline and 12 weeks after baseline. We aim to recruit 160 participants who experience mild to moderate depressive symptoms, defined as a Patient Health Questionnaire (PHQ-9) score of 5 to 15. This study is powered to detect a small between-groups effect, where no clinically relevant effect is defined as the effect size margin −0.25< d <0.25.

**Discussion:**

To our knowledge, this is the first study to investigate whether self-rated EMA of depressive symptoms could induce assessment reactivity among mildly depressed individuals.

**Trial registration:**

Netherlands Trial Register NTR5803. Registered 12 April 2016. http://www.trialregister.nl/trialreg/admin/rctview.asp?TC=5803.

## Background

Daily, repeated measurements of mental health symptoms, also known as experience sampling or ecological momentary assessment (EMA), enables clinicians, researchers and patients to monitor psychological processes in real time. EMA is usually operationalised as active monitoring, in which patients respond to prompted or self-initiated items or questions [1]. EMA involves repeated self-report assessments of a current state, such as daily assessments of mood. Several advantages of active EMA for assessing mental health problems, such as depression, have been noted [2]: absence of recall bias; sensitivity to mood fluctuations [3]; and real-time insight into treatment response, which can also be used as feedback to individual patients (e.g. [4]). Several studies have employed smartphones for EMA of depressive symptoms (e.g. [5–9]).

Active EMA may not only measure, but also influence mental health symptoms, which is known as assessment reactivity. Studies on alcohol abuse interventions show that repeated assessments draw attention to the monitored behaviour, which can identify problematic behaviour and highlight personal responsibility [10]. In that sense, EMA is similar to a brief intervention and can have a positive influence on treatment outcome [11]. Another type of reactivity is response fatigue, which is a declining response rate or declining response accuracy over time (e.g. [12]). A declining response accuracy could be observed by a declining correlation between a repeated measure and another measure that assesses a theoretically associated construct [12].

In the field of depression, EMA reactivity has received little attention. Kramer et al. [13] found that EMA of positive and negative affect may have a beneficial effect on depressive symptoms after 7 weeks, although the effect had disappeared at the 6-month follow-up [13]. EMA was conducted alongside pharmacotherapy in that study and the EMA was short and intensive, i.e. over 10 self-rated items, each of which had to be rated 10 times a day for 5 consecutive days and for 5 more consecutive days a few weeks later [13]. Positive and negative affect are related to depression, so reactivity to EMA of depressive symptoms may follow a similar pattern as was found by Kramer et al.. Little is known about reactivity to EMA of depressive symptoms when conducted for a longer consecutive period, such as 12 weeks.

This study aims to investigate whether EMA of depressive symptoms induces assessment reactivity. First, we will investigate whether EMA of depressive symptoms during a 12-week period has an effect on depressive symptoms measured by a retrospective questionnaire. Secondly, we will investigate whether response fatigue affects the EMA ratings. Response fatigue will be operationalised as response rate over time and correlations with measures of associated constructs. To minimise response burden, participants will monitor only one symptom and 1 to 3 times a day. Because depression is a multidimensional construct [14] we will conduct EMA of two core depression symptoms in two groups, where group 1 monitors mood and group 2 monitors how energetic they feel. Based on the literature we expect a small positive short-term effect of EMA on depressive symptoms.

## Methods

### Study design

This study is a 12-week randomised controlled trial among participants who experience mild to moderate depressive symptoms. The trial consists of three groups: group 1 carries out EMA of mood and completes a retrospective questionnaire; group 2 carries out EMA of how energetic they feel and completes a retrospective questionnaire; group 3 is the control group, which completes only the retrospective questionnaire. The retrospective questionnaire is the Centre for Epidemiologic Studies Depression scale (CES-D) [15], which assesses depressive symptoms. The CES-D is administered at baseline (T0), 6 weeks after baseline (T6) and 12 weeks after baseline (T12).

### Study population and inclusion criteria

We aim to recruit 160 adult (18+) participants who experience mild to moderate depressive symptoms among college students and users of mental health websites. We define mild to moderate depressive symptoms as a PHQ-9 score of 5 to 15 [16]. All participants are required to own a smartphone that runs the Android operating system, version 4.0 or later, because the EMA application runs only on that platform. Recruitment within a student population and among website users will ensure that many of the interested individuals own a smartphone and are used to installing and using apps.

### MoodMonitor, a self-monitoring application

Participants in group 1 and 2 install the MoodMonitor application on their smartphones, which conducts EMA of mood and energy level. This app has been developed by the E-Compared consortium [8]. Every day, the participant will receive one notification on his/her smartphone at a random time point between ten o’clock in the morning and ten o’clock in the evening. This notification directs the participant to the question ‘How is your mood right now?’ (group 1) or ‘How energetic do you feel right now?’ (group 2), which the participant can answer on a visual analogue scale from 1 (worst) to 10 (best) with a precision of 1 digit after the decimal point, e.g. 8.1. The notification remains accessible until the question is answered. If a notification remains unanswered, it is replaced when the next notification is sent. The measurement will be time stamped, i.e. the system records the exact time when the participant enters a rating, in addition to the time when the notification was sent. Furthermore, participants are free to provide a rating at any time they want by opening the app. During week 1 and week 12, the participant rates his/her mood three times a day instead of just once, in order to measure mood fluctuations during the day. The entered ratings are instantly visible to the participants on a graph which they can access through the MoodMonitor application.

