### Analyses

The primary outcome is the effect of EMA on depressive symptoms as measured by the CES-D at T6 and T12, comparing both EMA groups with the control group. To test this on all available data, we will conduct a mixed models repeated measures regression analysis, with T6 and T12 CES-D data as the dependent variable, and baseline CES-D scores, group (1, 2, 3), time (T6, T12) and the time*group interaction as independent variables. Effects will be expressed in terms of percentage of variance explained and Cohen’s d (by dividing raw regression parameter point estimates and confidence intervals by the pooled CES-D standard deviation).

For our secondary analysis, we will examine the EMA response rate over time, which gives an indication of response fatigue. Response fatigue will also be analysed by assessing response accuracy, here defined as a declining correlation over time between theoretically associated measures. Literature has shown that mood swings are associated with higher depressive symptoms [23]. Therefore, we will analyse the variance of the EMA and its correlation with the CES-D scores, taking into account the EMA ratings of the two weeks prior to the CES-D (i.e. weeks 5 and 6 for T6 and weeks 11 and 12 for T12). A decreasing variance of EMA ratings (i.e. increasingly stable responses) will result in a decreasing correlation coefficient (*r*) with the CES-D scores if the CES-D scores do not decrease. This might indicate a decline in validity.

We will maintain a family-wise two-tailed *p*-value of .05 using the Holm-Bonferroni method [24]. IBM SPSS Statistics 23 [25] and R [26] will be used for all analyses.

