### Limitations

First, a change in retrospectively measured depressive symptoms could be attributed not only to a change in depression severity, but also to a change in response behaviour. If we find an effect, we can explore changes in response behaviour by testing the CES-D outcomes for measurement invariance [28]. Second, one of our secondary aims is to investigate response rate, but the response rate might be artificially high, because participants are given a monetary reward when they complete 80 % or more of the EMA prompts. This reward is necessary to answer the primary research question, because any effect of EMA can only be shown when participants conduct EMA.

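### The EMA answer window averages about 24 h in weeks 2–11 but about 8 h in weeks 1 and 12, so the response rate barely registers moderate slowing and is not comparable across weeks

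*Protocol article*

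**What the plan says.** All references are to the protocol article.

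- **Prompt schedule** (MoodMonitor section): each day brings "one notification on his/her smartphone at a random time point between ten o’clock in the morning and ten o’clock in the evening". The exception is "During week 1 and week 12, the participant rates his/her mood three times a day instead of just once". The spacing of the three within a day is not given.
- **How a prompt closes** (same section): "The notification remains accessible until the question is answered. If a notification remains unanswered, it is replaced when the next notification is sent".
- **What is recorded** (same section): "the system records the exact time when the participant enters a rating, in addition to the time when the notification was sent". Unprompted entries are also allowed: "participants are free to provide a rating at any time they want by opening the app".
- **Fatigue analysis** (Analyses): "we will examine the EMA response rate over time, which gives an indication of response fatigue". A second measure, response accuracy, is the change over time in the correlation between EMA variance and CES-D, using weeks 5–6 for T6 and weeks 11–12 for T12.
- **Acknowledged weakness** (Limitations): "the response rate might be artificially high, because participants are given a monetary reward when they complete 80 % or more of the EMA prompts". The reward is the only cause of inflation named there.

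**The concern.** A response rate depends on how long a prompt may be answered. Here that time is not a chosen constant. It is whatever gap the schedule leaves before the next prompt, and the schedule changes after week 1 and again before week 12.

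Two things can go wrong. In the long middle stretch the window is so wide that participants can reply much later than they used to with almost no change in the rate. At the two ends the window is about a third as long, so the rate can move although behaviour has not. The item asks about the present moment, so how soon people answer bears on the quality of the data.

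The Implications section intends to use signs of fatigue at T6 and T12 to recommend how long EMA should run. A rate that is flat in the middle and depressed at the end for mechanical reasons could mislead that recommendation in either direction.

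**Working it through.** The article gives no expected response rate and no reply delay, so there is no figure of its own to reproduce. The delay distributions below are assumptions.

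**Step 1. Length of the answer window.**

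Weeks 2–11, one prompt a day at a uniform time between 10:00 and 22:00: the gap is G = 24 + U2 − U1 hours, with U1 and U2 uniform on 10 to 22. The mean is 24 h, the SD 4.9 h, the range 12 to 36 h, and the 5th to 95th percentile 15.8 to 32.2 h.

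Weeks 1 and 12, reading three ratings a day as three prompts: the mean gap is 24/3 = 8 h. The median gap depends on spacing, which is assumed: 4.4 h for three independent uniform times, 5.2 h for one prompt in each 4-hour block.

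**Step 2. Response rate when any answer before replacement counts.**

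Rate = P(delay < G), supposing every prompt would eventually be answered. For an exponential delay with mean m and one prompt a day,

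P(unanswered) = exp(−24/m) × [sinh(6/m)/(6/m)]².

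- Median 4 h: m = 4/ln 2 = 5.77 h. Then exp(−24/5.77) = 0.0156, the squared bracket is 1.416, and the product is 0.022. The rate is 97.8%.
- Mean 6 h: 0.0183 × 1.381 = 0.025, so the rate is about 97%.
- Mean 12 h: 0.1353 × 1.086 = 0.147, so the rate is about 85%.

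**Step 3. Sensitivity to slowing, weeks 2–11** (simulated gaps).

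| Median delay | Exponential | Lognormal, log-SD 1.0 | Lognormal, log-SD 1.5 |
|---|---|---|---|
| 0.5 h | 100% | 100% | 99.4% |
| 2 h | 99.9% | 99.2% | 94.8% |
| 4 h | 97.8% | 95.8% | 87.9% |
| 8 h | 86.3% | 85.4% | 76.1% |

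An eightfold slowing, from 0.5 h to 4 h, costs 2.2, 4.2 and 11.5 points respectively. For contrast, the share answered within a fixed 1 h, 1 − 2^(−1/median) under the exponential, goes from 75% to 16%.

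**Step 4. Comparability across weeks with behaviour held constant** (median delay 2 h).

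| Delay model | Weeks 1 and 12, uniform times | Weeks 1 and 12, 4-h blocks | Weeks 2–11 |
|---|---|---|---|
| Exponential | 69.5% | 80.3% | 99.9% |
| Lognormal, log-SD 1.0 | 67.9% | 79.6% | 99.2% |
| Lognormal, log-SD 1.5 | 64.9% | 73.6% | 94.8% |

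**Step 5. What this would do to a T6 versus T12 comparison.** Suppose the rate were summarised over the same two-week periods as the accuracy measure. Weeks 5–6 hold 14 prompts; weeks 11–12 hold 7 + 21 = 28. Under the exponential with a constant 2 h median, T6 reads 99.9%. T12 reads (7 × 99.9 + 21 × 69.5)/28 = 77.1% with uniform times, or (7 × 99.9 + 21 × 80.3)/28 = 85.2% with blocks. The apparent fall of about 15 to 23 points comes from the schedule alone.

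**The case against.** **The scoring rule is inferred.** The MoodMonitor section describes how the app behaves; the Analyses section does not say what counts as a valid response. A time limit could be set in an analysis plan that is not shown, and the time stamps would allow it. This stands as a caution: the point rests on the natural reading that a prompt answered before replacement counts. It remains more than missing detail, because the article itself fixes a window that changes length by week and names the resulting rate as the fatigue indicator.

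**Slower replying is not fatigue by the article's definition.** The Background defines fatigue as a declining rate or declining accuracy. That is correct, and latency would be an addition. But the rate itself depends on the window, so its trend is distorted even within that definition.

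**Stronger readings that the article does not support.**

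- A reader might infer that fatigue would go undetected. It would not: wholly ignored prompts lower the rate directly, the rate does fall once median delay reaches about 8 h (76–86%), and the accuracy measure is separate.
- A reader might infer that participants could save up prompts and answer them together. They cannot, because each new prompt replaces the one before it.
- A reader might apply the 24 h window, and the false reassurance it suggests, to the whole trial. In weeks 1 and 12 the window is about 8 h, and in week 12 the distortion runs towards apparent fatigue.
- A reader might conclude that late or self-initiated ratings are invalid. The question asks about the current state whenever it is answered, and self-initiated entry is part of the design.

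**Any particular cut-off is a preference.** Agreed. Nothing in the article points to 60 minutes or any other value, and a short limit would count someone in class or at work as not responding.

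**Conclusion.** The point holds for a secondary aim. As written, the response rate over time hardly registers moderate slowing in weeks 2–11 (a loss of about 2 to 12 points for an eightfold slowing). It also cannot be compared between weeks 1 and 12 and the weeks between (about 70–80% against nearly 100% at a constant 2 h median delay, exponential). Fatigue would be under-detected in the middle of the trial and could be mimicked in week 12.

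The window means follow from the stated schedule, taking the random times as uniform and three ratings a day as three prompts in both EMA groups. The rates also rest on assumed delay distributions without allowance for sleep, on assumed within-day spacing, and on every prompt being answered eventually. If a share q is ignored whatever the delay, each rate is multiplied by (1 − q). The direction was the same under every delay shape and spacing tried; the exact size is not knowable from the article. The Limitations section does not cover the problem, since it attributes inflation to the reward alone.

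**What to change.** 1. Compute the fatigue response rate with one common response window for all weeks, chosen before the data are seen and no longer than the shortest spacing between prompts, with one or two sensitivity windows. State the within-day spacing used in weeks 1 and 12. If the three times are unconstrained, some gaps will be very short (under uniform times, 5% are below about 0.3 h). In that case, leave out of the denominator any prompt whose successor was sent inside the window.
2. Add reply latency by week as a companion measure, from the prompt and rating times already stored, treating replacement of a prompt as censoring.
3. Do not count self-initiated ratings as responses to prompts. Report their weekly number separately, and repeat the EMA variance analysis without them as a sensitivity analysis.
4. Keep answered-before-replacement as the rule for the voucher, so nothing changes for participants.
5. Name the changing window beside the reward in the Limitations section.

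The cost is analysis wording and a little extra work; no new data are needed. The reported response rate will be lower, and the sensitivity analysis of variance will rest on fewer ratings.

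### The T6 and T12 windows for EMA variance use different prompt schedules, so this secondary fatigue contrast is confounded with schedule

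*Protocol article*

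**What the plan says.** All references are to the protocol article.

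- **Schedule** (Methods, *MoodMonitor, a self-monitoring application*). The default is one prompt a day: "Every day, the participant will receive one notification on his/her smartphone at a random time point", between 10:00 and 22:00. The exception is "During week 1 and week 12, the participant rates his/her mood three times a day instead of just once", and its stated purpose is "in order to measure mood fluctuations during the day".
- **Lapse of prompts** (same section). "If a notification remains unanswered, it is replaced when the next notification is sent".
- **Self-initiated ratings** (same section). "participants are free to provide a rating at any time they want by opening the app".
- **Response rate** (Methods, *Analyses*). "we will examine the EMA response rate over time, which gives an indication of response fatigue".
- **Response accuracy** (same section). The variance of EMA ratings is correlated with CES-D over "weeks 5 and 6 for T6 and weeks 11 and 12 for T12". Falling variance, and with it a falling correlation when CES-D does not fall, is read as a possible loss of validity.
- **Use of the result** (*Implications*). Signs of fatigue at T6, T12 or both are to support advice on how long EMA should run.
- **Acknowledged limits** (*Limitations*). For the response rate, only the monetary reward is named.

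**The concern.** The denser weeks were added to capture within-day fluctuation, not to study fatigue. One of them falls inside the T12 window and neither falls inside the T6 window. A change in variance, or in its correlation with CES-D, from T6 to T12 therefore reflects two things at once: any change in how carefully people answer, and a change in how often and how closely in time they are sampled.

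The lapse rule raises a related problem for the response rate. Three prompts a day leave less time to answer each one, so unchanged behaviour can give a lower rate per prompt in week 12 than in mid-study.

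At stake is the trial's second operationalisation of reactivity, and the advice on EMA duration drawn from it.

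**Working it through.** **1. The plan's own figures.** The article gives no calculated figure for the fatigue analyses. Its only one is the primary sample size. A repeated-measures within-between test with f = 0.25/2 = 0.125, 3 groups, 3 waves, r = .65 and epsilon = .8 has noncentrality 120 × 3 × 0.125² × 0.8 / 0.35 = 12.86 and power 0.851 at N = 120. Then 120/(1 − 0.25) = 160. The figure reproduces and plays no part below.

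**2. Prompt counts.** T6 window: 14 days × 1 = 14. T12 window: 7 × 1 + 7 × 3 = 28, of which 21 fall in week 12. Whole study: 21 + 70 + 21 = 112. The week-12 sentence mentions only mood. The three-a-day schedule is taken to apply to both EMA groups, because the Background says participants monitor one symptom one to three times a day.

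**3. Expected variance with no fatigue.** For ratings of constant variance, the expected sample variance is that variance × (1 − mean pairwise correlation). If ratings correlate by w within a day and by 0 between days, T6 has no within-day pairs. T12 has 7 × 3 = 21 such pairs among 28 × 27/2 = 378, so the T12/T6 ratio is 1 − (21/378)w = 1 − 0.056w. A second model lets the correlation decay between days as w × 0.5^(days apart).

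**4. Correlation with CES-D.** Let e and v be the mean and sampling variance of the sample variance (normal ratings, true variance 1), and CV the between-person coefficient of variation of true variance. The observed correlation is .40 × √[CV²e² / (CV²e² + v(1 + CV²))]. With w = 0, v = 2/13 = 0.154 at T6 and 2/27 = 0.074 at T12. At CV 0.5 this gives .40 × √(0.25/0.442) = .301 and .40 × √(0.25/0.343) = .342.

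| w | Variance ratio T12/T6 (no decay term; decay 0.5) | r, T6 to T12, CV 0.3 | CV 0.5 | CV 0.8 |
|---|---|---|---|---|
| 0 | 1.000; 1.000 | .236 to .290 | .301 to .342 | .339 to .367 |
| 0.3 | .983; .978 | .236 to .282 | .301 to .336 | .339 to .363 |
| 0.5 | .972; .961 | .236 to .268 | .301 to .326 | .339 to .356 |
| 0.7 | .961; .944 | .236 to .250 | .301 to .312 | .339 to .347 |

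The r columns use no between-day correlation. With the decay model the rises stay in the same range. The variance falls by 0 to 6%; r rises by about .01 to .05. All prompts are taken as answered, with no self-initiated ratings.

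**5. Response rate with no fatigue.** With one prompt a day the answering window is 24 h plus the difference of two random times between 10:00 and 22:00, so 12 to 36 h. With three a day, assuming one per 4-hour block, the mean gaps are 4, 4 and 16 h. The probability of answering is 1 − exp(−gap × ln 2 / median latency), averaged over simulated gaps. Weeks 11-12 pooled per prompt is (7 × one-a-day rate + 21 × three-a-day rate)/28.

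| Assumed median latency | One-a-day weeks (incl. weeks 5-6) | Weeks 1 and 12 | Weeks 11-12 pooled |
|---|---|---|---|
| 1 h | 1.00 | 0.92 | 0.94 |
| 2 h | 1.00 | 0.80 | 0.85 |
| 4 h | 0.98 | 0.63 | 0.72 |
| 8 h | 0.86 | 0.44 | 0.55 |

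If the three prompts fall at random between 10:00 and 22:00, the rates in weeks 1 and 12 are 0.81, 0.70, 0.56 and 0.40. Week 1 equals week 12 in every row, weeks 2 to 11 are flat, and a straight line over weeks 1 to 12 has slope 0.000.

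**The case against.** A reader might infer more than the document supports, in four ways.

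- **That every comparison over time is confounded, and that the week-12 response rate must collapse.** The article fixes no response-rate contrast, denominator or time grid, and may leave these to a fuller plan. Week 1 shares week 12's schedule and is lowered equally. Only a comparison of week 12 with one-a-day weeks is exposed. This objection stands.
- **That the size of that drop is known.** The document gives no latency and no timing rule for the three daily prompts. The model treats every non-response as delay; if people either answer at once or ignore a prompt altogether, frequency matters little. This stands too: the mechanism is sound, the size is not established.
- **That the accuracy analysis would imitate fatigue.** The expected variance may fall slightly, but the correlation, which is how the article defines accuracy, moves upward. The artefact hides fatigue rather than creating it. It is also small beside sampling error: with about 2 × 40 = 80 EMA completers, the standard error of one correlation is about 1/√77 = .11 (Fisher scale). This limits the weight of the point but does not remove a systematic shift.
- **That the bonus removes the incentive in week 12.** 80% of 112 is 89.6, and 91 prompts have been issued by the end of week 11. So the bonus is secured before week 12 only by someone who has missed at most one of 91, and the Limitations section already says the reward may distort the response rate.

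What no objection removes is the mismatch of the variance windows. They are written into the Analyses section, so this is a stated rule and not a detail deferred elsewhere.

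**Conclusion.** The point holds for the variance and correlation analysis: 14 prompts on one schedule are set against 28 on two, so the T6/T12 contrast cannot separate fatigue from sampling density. Under the assumptions shown (within-day correlation 0 to 0.7, true correlation .40, CV of true variance 0.3 to 0.8, no fatigue), the variance falls by 0 to 6% and the correlation rises by about .01 to .05. None of these assumptions comes from the document. The rise would partly mask the decline the plan looks for.

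For the response rate the point is conditional. Week 12 against one-a-day weeks can show a drop without fatigue, of a size that depends on unknown latency; comparisons within one schedule are sound.

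Only secondary analyses are affected. The primary CES-D analysis and the sample size stand. The change is worth making because it is cheap and the *Implications* section relies on this contrast.

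**What to change.** Leave the prompt schedule as it is and change the wording of the *Analyses* section:

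1. Compute the T12 variance with one randomly chosen prompted rating per day in week 12, so that each window holds at most 14 prompted ratings, one a day.
2. Exclude self-initiated ratings from both windows.
3. Assess response rate only within one schedule: week 1 against week 12, and the trend over weeks 2 to 11.

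Prompt and answer times are already recorded, so nothing changes in the app, data collection or sample size. The cost is that some week-12 ratings go unused in the variance comparison, which becomes slightly less precise. They remain available for their stated purpose of describing within-day fluctuation.
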